# A multicenter noninferior randomized controlled study of sentinel lymph node biopsy alone versus sentinel lymph node biopsy plus lymphadenectomy for patients with stage I endometrial cancer, INSEC trial concept

**DOI:** 10.1186/s12885-023-11226-1

**Published:** 2023-12-02

**Keywords:** Endometrial cancer, Sentinel lymph node, Indocyanine green, Near-infrared fluorescence imaging, Lymphadenectomy

## Abstract

**Background:**

Up to the present time, there has remained a lack of strong evidence as to whether sentinel lymph node biopsy can replace lymphadenectomy for early endometrial cancer. The traditional surgery for endometrial cancer includes pelvic lymphadenectomy and paraaortic lymph node resection, but complications often seriously affect patients’ quality of life. Two randomized controlled trials with large samples have proved that lymphadenectomy does not improve the overall recurrence rate and survival rate of patients. On the contrary, it increases the incidence of complications and even mortality. The current trial is designed to clarify whether sentinel lymph node biopsy can replace lymphadenectomy for early endometrial cancer patients with negative lymph nodes.

**Methods:**

This study is a randomized, open-label, multicenter and non-inferiority controlled clinical trial in China. Potential participants will be patients with pathologically confirmed endometrial cancer at the Zhejiang Cancer Hospital, Jiaxing Maternity and Child Health Care Hospital, and the First Hospital of Jiaxing in China. The total sample size for this study is 722.

Patients will be randomly assigned in a 1:1 ratio to two groups. Patients in one group will undergo sentinel lymph node biopsy + total hysterectomy + bilateral salpingo-oophorectomy ± paraaortic lymph node resection. Patients in the other group will undergo sentinel lymph node biopsy + total hysterectomy + bilateral salpingo-oophorectomy + pelvic lymphadenectomy ± paraaortic lymph node resection. The 3-year disease-free survival rate, overall survival rate, quality of life (use EORTC QLQ-C30 + QLQ-CX24), and perioperative related indexes of the two groups will be compared.

**Results:**

We expect to find that for patients with early endometrial cancer, the 3-year disease-free survival rate following sentinel lymph node biopsy with indocyanine green combined with near-infrared fluorescence imaging is similar to that following lymphadenectomy. The operation time, as well as incidence of pelvic lymphocyst, lymphedema of lower limb, and edema of vulva in patients who only undergo sentinel lymph node biopsy are expected to be significantly lower than in patients who undergo lymphadenectomy. The quality of life of patients who undergo sentinel lymph node biopsy alone will be significantly better than that of patients who undergo lymph node dissection.

**Conclusion:**

This will prove that the prognosis of sentinel lymph node biopsy alone with indocyanine green combined with near-infrared fluorescence imaging is not inferior to that of sentinel lymph node biopsy plus lymphadenectomy for early stage endometrial cancer with negative nodal assessment intraoperatively. In addition, sentinel lymph node biopsy alone with indocyanine green combined with near-infrared fluorescence imaging results in fewer surgical complications and gives patients better quality of life.

**Trial registration:**

chictr.org.cn, ChiCTR1900023161. Registered 14 May 2019, http://www.chictr.org.cn/edit.aspx?pid=38659&htm=4.

## Background

Endometrial cancer (EC) is one of the most common gynecological malignancies. The incidence rate is increasing each year. Lymph node metastasis is the main factor affecting prognosis while nodal status is extremely important in guiding adjuvant therapies [1–3]. The 5-year survival rates of patients with stage I non-metastatic endometrial cancer and patients with pelvic or paraaortic lymph node involvement are 90% and 44% ~ 52%, respectively [4].

The sentinel lymph node (SLN) is the first lymph node that a primary solid tumor must pass through when lymph node metastasis occurs. It reflects the state of lymph node metastasis in the whole region [5]. Indocyanine green (ICG) combined with near-infrared fluorescence imaging can accurately locate the sentinel lymph nodes of patients with early endometrial cancer, and then sentinel lymph node biopsy can be performed during the operation. If the frozen pathology is negative, the patient does not need lymphadenectomy. In addition, ICG combined with near-infrared fluorescence imaging has been proved to be superior to ^99^Tc, blue dye and other methods, especially for obese patients [6–9]. Most patients with endometrial cancer are obese, so this technology is very suitable for patients with early endometrial cancer.

Lymph node metastasis is the main type of metastasis in endometrial cancer. The evaluation of lymph node status and the selection of surgical methods are of great significance when formulating a treatment plan and predicting a prognosis. The traditional surgery for endometrial cancer includes pelvic lymphadenectomy and paraaortic lymph node resection, but complications often seriously affect patients’ quality of life. Two randomized controlled trials with large samples have proved that lymphadenectomy does not improve the overall recurrence rate and survival rate of patients. On the contrary, it increases the incidence of complications and even mortality [1, 2]. However, inclusion of large number of patients with low-grade, low stage disease potentially diluting the benefit of lymphadenectomy may be the limitations of the two trials. Extensive lymphadenectomy has significantly increased complications.

So far, there has been no consensus on whether sentinel lymph node biopsy can replace lymphadenectomy in the treatment of patients with early endometrial cancer. The following are the results of sentinel lymph node studies to date. In 2017, Lancet Oncology published the results of robotic sentinel lymph node biopsy (FIRES study) in patients with stage I endometrial cancer. The results showed that the sensitivity of sentinel lymph node biopsy in the diagnosis of lymph node metastasis was 97.2%, and the negative predictive value was 99.6% [10]. Some scholars express concern that sentinel lymph node mapping will miss isolated paraaortic lymph nodes, especially in patients with a high metastasis rate of paraaortic lymph nodes (such as high-grade and tumor-infiltrating deep muscle layer) [11]. To address this concern, Bogani et al. [12] conducted a meta-analysis of the clinical data of 3,536 patients with endometrial cancer who underwent sentinel lymph node biopsy (1,249 cases) or lymphadenectomy (2,287 cases). The results showed that the positive detection rate of pelvic lymph nodes in the sentinel lymph node mapping group was higher than that in the lymphadenectomy group (14.7%: 9.9%). There was no significant difference in the positive detection rate of paraaortic lymph nodes between the two groups. Also, there was no significant difference in the total recurrence rate (4.3%: 7.3%) or lymph node recurrence rate (1.2%: 1.7%) between the sentinel lymph node mapping group and the lymphadenectomy group. In addition, a study found that the sensitivity and negative predictive value of sentinel lymph node biopsy in patients with high-risk histological types of endometrial cancer were 95.0% and 98.6%, respectively. 89% of patients had at least one sentinel lymph node mapping. Of these, 58% were bilateral sentinel lymph nodes, 40% were unilateral sentinel lymph nodes, and 2% were isolated paraaortic lymph nodes [13]. Maria C. Cusimano and Sarah E. Ferguson underwent SENTOR trial and found the acceptable accuracy of sentinel lymph node mapping in high-grade endometrial cancer. Of 27 patients with nodal metastasis, sentinel lymph node mapping correctly identified 26 of them (96% sensitivity; 95% CI; 81%–100%) [14]. A study jointly carried out by Memorial Sloan-Kettering Cancer Center and the Mayo Clinic found that compared with lymphadenectomy, sentinel lymph node biopsy for endometrial cancer with deep myometrial invasion did not affect the tumor outcome, and the prognosis of lymph-node-negative patients was better, but this had nothing to do with the evaluation method of lymph nodes [15]. Sentinel lymph node mapping did not affect the prognosis of high-risk endometrial cancer [16]. Moreover, How et al. [17] systematically evaluated 5,348 patients in 48 studies. The results showed that the total detection rate of SLN detected by ICG combined with near-infrared fluorescence imaging was 94%, which was significantly higher than that by blue staining (86%) and radionuclide method (86%). 34 studies showed a total sensitivity of 94% and a negative prediction rate of 100%. Therefore, indocyanine green combined with near-infrared fluorescence imaging technology has a good clinical application prospect.

## Methods

### Trial design and surgical quality assurance

The INSEC study (ChiCTR1900023161) is a randomized, open-label, multicenter and non-inferiority controlled clinical trial in China. Potential participants will be patients with pathologically confirmed endometrial cancer at the Zhejiang Cancer Hospital, Jiaxing Maternity and Child Health Care Hospital, and the First Hospital of Jiaxing in China. Patients will be randomly assigned in a 1:1 ratio to two groups, Arm A and Arm B (Fig. 1). Patients in Arm A will undergo sentinel lymph node biopsy (SLNB) + total hysterectomy (TH) + bilateral salpingo-oophorectomy (BSO) ± paraaortic lymph node resection. Patients in Arm B will undergo SLNB + TH + BSO + pelvic lymphadenectomy (PL) ± paraaortic lymph node resection.

**Fig. 1 Fig1:**
[figure not shown]
Study flow chart. SLNB: Sentinel lymph node biopsy; TH: Total hysterectomy; BSO: Bilateral salpingo-oophorectomy; PL: Pelvic lymphadenectomy; DFS: Disease-free survival; OS: Overall survival

### Qualification of surgeons

So far, there is no consensus on whether sentinel lymph node biopsy can replace lymphadenectomy in the treatment of patients with early endometrial cancer. The need for qualification and training of surgeons involved in these studies is particularly important, especially on minimally invasive surgery techniques and cervical ICG injection. The current study asks that surgeons involved in the study have operated on more than 50 cases of endometrial cancer by independent minimally invasive surgery and injected ICG into the cervix in more than 30 cases. In addition, it is suggested that the participating center should be a gynecological oncology center with sufficient patients, and should have sentinel lymph node ultra-staging technology. Then, it will be carefully evaluated in stratification. We look forward to the prognostic data of the study in a few years.

### Inclusion criteria

Age is 18–70Endometrial diagnostic curettage pathology suggests endometrioid adenocarcinoma (including cancerization)Pelvic magnetic resonance imaging (MRI) shows that the lesion is limited to the uterine bodyGynecological examination: uterus less than 2 months pregnant (length ≤ 10 cm, width ≤ 8 cm)No suspicious nodes on abdominal computed tomography (CT), according to Response Evaluation Criteria in Solid Tumours (RECIST) 1.1Performance Status-Eastern Cooperative Oncology Group (PS-ECOG) 0–1 pointsBlood routine and biochemical examination: leukocyte ≥ 4000 cells mm3, platelet ≥ 10000/mm3, hemoglobin ≥ 8.0 GM/dl, serum creatinine ≤ 1.3 mg/dl, serum urea nitrogen ≤ 1.5 mg/dlPatient has the ability to sign informed consent and comply with follow-up actionsOnly patients undergoing minimally invasive surgery using ICG combined with near-infrared fluorescence imaging are included.

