### Statistical methods

Disease-free survival and overall survival curves will be evaluated using the Kaplan Meier method. The survival difference between the two groups will be analyzed by log-rank method. The analysis of prognostic factors will use appropriate regression models (such as Cox model). Efficacy indicators will be compared through intention-to-treat analysis including all randomized patients. Toxicity will be analyzed based on the treatment received. The 95% confidence interval of the difference between the two groups will be calculated at the same time. Descriptive statistical analysis will be used for treatment-related adverse events and quality of life scores (QLQ-C30, QLQ-CX24). The normality and equality of differences between the two groups of continuous variables will be evaluated. Discrete variables (such as presence/absence of postoperative infection) will be aggregated by frequency/proportion.

For continuous variables, analysis of variance and/or regression analysis will be used as appropriate. If the assumptions of these tests are violated, an alternative nonparametric test method will be used. Differences in discrete variables between groups will be assessed by chi square test. The risk proportional regression model will be used to explore the prognostic factors such as age, degree of differentiation, lymph node metastasis, and PS-ECOG.

The hypothesis H0: “Sentinel lymph node biopsy alone is not inferior to sentinel lymph node biopsy plus lymphadenectomy for early stage endometrial cancer with negative nodal assessment intraoperatively.”

In the current study, there are three patient groups: intention-to-treat (ITT) group, including all randomized patients who signed the consent form; a group of those in serious violation of the protocol, excluded from the efficacy analysis; and a safe population of all randomized patients who at least start the study treatment.

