### Sample size

The primary endpoint of this study is 3-year DFS. According to the results of previous research, patients with stage I endometrial cancer who received laparoscopy had 3-year DFS of 88.6% [18]. It is assumed that the 3-year DFS of the reference group and the experimental group is 88%, and the non-inferior boundary value is 8%. Considering the 20% loss of follow-up rate, 361 subjects need to be included in each group to ensure 80.0% power using a 2-sided log-rank test with a type I error rate of 0.05 to reject the null hypothesis. The total sample size of this study is 722 and the number of outcome events in each group is 40. The sample size calculation was done using the PASS software (version 11.0).

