### Trial status

This study was approved by the Institutional Review Board of the Zhejiang Cancer Hospital in Zhejiang, China, in 18 December 2018. The trial was registered on chictr.org.cn and a registration number was obtained. Recruitment of participants started in January 2019. The last participant will be expected to achieve the primary endpoint (3-year disease-free survival) in 2028. The protocol version number was 5.0 and the protocol version date was 16 Jun 2022.

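### The urea nitrogen entry limit of 1.5 mg/dl cannot be the one applied, and the platelet limit of 10000/mm3 is probably a misprint too; both need reconciling with protocol version 5.0

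*Protocol article*

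**What the plan says.** The Inclusion criteria section of the protocol article sets blood-count and biochemistry limits in a single item. It opens with a leukocyte floor of 4000 cells/mm3 and continues "platelet ≥ 10000/mm3, hemoglobin ≥ 8.0 GM/dl, serum creatinine ≤ 1.3 mg/dl, serum urea nitrogen ≤ 1.5", the last figure also in mg/dl. The figures are complete, with units, in running text; nothing is blacked out or lost from a table.

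No other section gives a different value, a multiple of a laboratory reference limit, or a waiver. The Exclusion criteria contain nothing on platelets or coagulation. Preoperative investigation asks for a whole blood count, biochemistry and each institution's usual preoperative tests, and sets no threshold for any of them.

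Three other statements bear on the point. Under Sample size: "The total sample size of this study is 722". Under Trial status: "Recruitment of participants started in January 2019", with the protocol then at version 5.0. Under Statistical methods, efficacy is to be compared by intention to treat in all randomized patients, while the same section also lists "a group of those in serious violation of the protocol, excluded from the efficacy analysis".

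**The concern.** An inclusion limit is a decision threshold: each patient passes or fails on it, and monitors, the ethics committee and readers judge eligibility by it. A urea nitrogen ceiling of 1.5 mg/dl lies well below the values expected in adults, so by the letter almost nobody could enter. It also sits oddly beside a creatinine ceiling of 1.3 mg/dl in the same item and unit, which is on an ordinary scale.

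The platelet floor errs the other way. It can be applied, but as printed it screens out almost nobody before hysterectomy with or without lymphadenectomy.

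At stake are whether eligibility can be verified at all against the public criteria and, for platelets, whether an entry limit with a safety bearing is stated correctly.

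**Working it through.** The article states no derived figure here that could be reproduced, so this is a plausibility check.

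**Inputs from the article**
- Urea nitrogen ≤ 1.5 mg/dl, creatinine ≤ 1.3 mg/dl, platelets ≥ 10000/mm3 (Inclusion criteria).
- 722 patients (Sample size); recruiting since January 2019 (Trial status).

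**Assumptions (not in the article)**
- Central 95% range of adult urea nitrogen: 5–25, 6–20, 7–20 or 8–23 mg/dl, with a normal or a log-normal shape.
- Lower reference limit for platelets: 100000–150000/mm3.
- Conversion for urea nitrogen: 1 mmol/L ≈ 2.8 mg/dl.

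**Step 1. Share of patients meeting urea nitrogen ≤ 1.5 mg/dl**

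For a range L to U:
- Normal shape: mean = (L + U)/2, SD = (U − L)/3.92, share = Φ((1.5 − mean)/SD).
- Log-normal shape: the same on the log scale, with ln 1.5 = 0.405.

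For 5–25 mg/dl:
- Normal: mean 15, SD 20/3.92 = 5.10, z = (1.5 − 15)/5.10 = −2.65, share 0.41%.
- Log-normal: log mean (ln 5 + ln 25)/2 = 2.414, log SD (ln 25 − ln 5)/3.92 = 0.411, z = (0.405 − 2.414)/0.411 = −4.89, share 5 × 10⁻⁷.

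| Assumed range (mg/dl) | Normal shape | Log-normal shape |
|---|---|---|
| 5–25 | 0.41% | 5 × 10⁻⁷ |
| 6–20 | 0.064% | 5 × 10⁻¹¹ |
| 7–20 | 0.015% | below 10⁻¹⁴ |
| 8–23 | 0.013% | below 10⁻¹⁴ |

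The size of the tail depends heavily on the shape, so the log-normal figures should not be quoted alone. The conclusion is the same in all eight cells.

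**Step 2. What that means for recruitment**

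In the most generous cell, 722 × 0.00407 ≈ 3, so about 3 of 722 unselected patients would meet the limit. To enrol 722, about 722/0.00407 ≈ 177,000 would have to be screened, before any other criterion is applied.

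**Step 3. Does a different unit rescue it?**

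1.5 mmol/L × 2.8 = 4.2 mg/dl, below the lower end of every assumed range. For 5–25 mg/dl and a normal shape, z = (4.2 − 15)/5.10 = −2.12, a share of 1.7%; the other cells are lower. It does not.

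**Step 4. Fit with the creatinine limit**

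The ratio of the two renal ceilings is 1.5/1.3 = 1.15. Even the lowest value in any assumed range, 5 mg/dl, is 5/1.5 = 3.3 times the urea nitrogen ceiling. The two limits do not describe the same level of renal function.

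**Step 5. Platelets**

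10000/100000 = 10% and 10000/150000 = 7% of the assumed lower reference limit. The article has no second platelet figure to set against this, so implausibility is all that can be shown.

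**The case against.** **The printed urea nitrogen limit is probably not the operative one.** Sites that have recruited since 2019 can hardly be applying a limit that nobody meets, so the likeliest explanation is a transcription error in the article. This stands. Whether version 5.0 carries the same figure cannot be seen. The statement that almost no one qualifies therefore describes the printed line, not a demonstrated effect on enrolment, and re-checking randomized patients is only conditionally needed.

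**The efficacy analysis.** A reader might infer that nearly every randomized patient becomes a serious protocol violator and drops out of the efficacy analysis, leaving the non-inferiority comparison arbitrary. The article does not support this. Statistical methods keeps an intention-to-treat comparison of all randomized patients, and it neither defines a serious violation nor ties it to laboratory entry limits. How loosely that excluded group is described is a separate matter and would be the same with any urea nitrogen figure.

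**Platelets.** This limit can be applied and contradicts no other figure in the article. The institutional preoperative work-up is a further check, although no threshold is attached to it. A reader might also infer that the low floor distorts the comparison of blood loss or complications. It acts on both arms before 1:1 randomization, so it creates no bias between them. What remains is a probable misprint with a safety bearing, held with less confidence than the urea nitrogen point.

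**Outside knowledge.** The reference ranges are assumptions. That is true, but the urea nitrogen conclusion does not change across the ranges and shapes tried.

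**Conclusion.** The point holds in two parts of unequal strength.

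- **Urea nitrogen, firm.** At most about 0.4% of patients would meet the printed limit under the assumed ranges (1.7% if the unit were mmol/L). That cannot be squared with a 722-patient trial already recruiting, nor with the creatinine limit beside it. The criterion is wrong as printed.
- **Platelets, probable.** At 7–10% of an assumed lower reference limit, and with no other platelet or bleeding criterion listed, the figure is likely a misprint. The article alone cannot prove it.

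The ranges are taken to be roughly right for women with endometrial cancer aged 18–70. The endpoint, margin, sample size, power and analysis of all randomized patients are untouched, and no bias between arms follows.

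**What to change.** 1. Compare both limits, values and units, with protocol version 5.0 and with the limits each site actually used at screening.
2. If version 5.0 differs from the article, publish a correction. If it prints the same figures, amend the protocol and publish the corrected limits.
3. Only if the printed figures stand in version 5.0 or were applied at sites, check the recorded laboratory values of randomized patients against the corrected limits.
4. In every case, keep all randomized patients in the intention-to-treat analysis and class no one as a serious violator on the misprinted limits.

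The values are for the sponsor to supply; none is suggested here. The cost is a correction notice or a short amendment, plus, if step 3 applies, a query of laboratory values already recorded.

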### Exclusion criteria

Pathology suggests non-endometrioid adenocarcinomaPregnancy or lactationPatients with synchronous cancerReceived neoadjuvant chemotherapy and/or radiotherapyAllergic reaction to ICGSevere cardiopulmonary vascular disease leading to intolerance to surgeryMental illnessPatient does not agree to sign informed consentCervical stroma invasionIntraoperative sentinel lymph nodes were not consistent with those in the group (no sentinel lymph node identified was found above one side, and/or frozen pathological metastasis of lymph nodes was found)

### Operation procedures

All patients were required to undergo pelvic MRI and upper abdominal CT examination before operation. Patients for whom preoperative endometrial diagnostic curettage pathology suggested endometrioid adenocarcinoma were selected for operation. Informed consent was signed according to the admission and discharge criteria.Indocyanine green was injected into the cervix at 3 o'clock and 9 o'clock positions (Indocyanine green concentration 1.25 mg/ml, 0.5 ml for each site 1–3 mm Superficial injection and 1–2 cm deep injection, 1 ml for each side). SLN was detected by near infrared fluorescence imaging.Operation modePreoperative prophylactic antibiotics should be given at least 30 min before skin cutting;In the low lithotomy position, the patient’s arm is parallel to the patient or placed on the patient’s chest;Considering the wide variety of instruments available for the operation, the choice of minimally invasive surgical instruments will be decided by the surgeon.The minimally invasive abdominal technique and the number of trocar ports used for the operation depend on the judgment of the surgeon.Ascites exfoliated cells will be sent for examination. All peritoneal surfaces should be thoroughly examined, including direct examination of the diaphragm. The location of any metastatic disease should be recorded in the surgical report and biopsy should be performed to confirm the diagnosis.Additional instructionsIf the suspected enlarged lymph nodes are detected under minimally invasive surgery, then the enlarged lymph nodes are sent to frozen pathology for definite metastasis. The patient will be treated with TH + BSO + PL ± paraaortic lymph node resection, and excluded from the group.If no sentinel lymph node is found, TH + BSO + PL ± paraaortic lymph node resection will be performed and the patient will be excluded from the group.If only unilateral sentinel lymph nodes are found, the patient will be excluded from the group and TH + BSO + PL ± paraaortic lymph node resection will be performed.If there are no suspicious enlarged lymph nodes on either side of the pelvic and abdominal cavity under minimally invasive surgery, and bilateral sentinel lymph nodes are developed, the developed SLN shall be removed and frozen pathology shall be performed during the operation. If the frozen pathology indicates that SLN is negative, they will be randomized into the experimental group or the reference group. Experimental group: SLNB + TH + BSO ± paraaortic lymph node resection; Reference group: SLNB + TH + BSO + PL ± paraaortic lymph node resection. If the frozen pathology of SLN is positive, the patient shall be excluded from the group and treated with TH + BSO + PL ± paraaortic lymph node resection.Sentinel lymph node ultra-staging will be performed by postoperative pathology: routine Hematoxylin and Eosin (H & E) staining will be performed first. If the result is negative, two adjacent pieces of paraffin at an interval of 5 μm to 50 μm slices will be cut and stained with H & E and cytokeratin AE1/AE3 respectively.Description of paraaortic lymph node resection: 1) Paraaortic sentinel lymph nodes are developed. The developing lymph nodes are removed and sent to frozen pathology during the operation. If the frozen pathology is negative and the patient has high-risk factors (lymph-vascular space invasion, deep muscle invasion, G3), the paraaortic lymph node resection needs to be done reaching at least the level of the inferior mesenteric artery, and the surgeon will decide whether to reach the level of the renal vein. If the frozen pathology is negative and the patient has no high-risk factors, paraaortic lymph node resection need not be performed. If the frozen pathology is positive, the patient shall be excluded from the group. Paraaortic lymph node dissection shall be performed to reach at least the level of the inferior mesenteric artery, and the surgeon will decide whether to reach the level of the renal vein. 2) No paraaortic sentinel lymph node is developed. Patients without high-risk factors need not undergo paraaortic lymph node resection. Patients with high-risk factors (lymph-vascular space invasion, deep myometrial invasion, G3) need to undergo paraaortic lymph node resection to reach at least the level of the inferior mesenteric artery, and the surgeon will decide whether to reach the level of the renal vein.
